**EXPECTED OUTCOME**

It is expected that pregnant diabetics treated with metformin will have a lower 2HPG levels at the end of the study than those treated with insulin. The primary outcome is the difference in the 2HPG level between the metformin and insulin group. The rationale for selecting 2HPG is that by its mechanism of action, metformin is expected to have a more significant blood glucose lowering effect in the postprandial period than the fasting period. Hyperglycaemia in the prandial period is related to insufficient suppression of hepatic glucose output, poor insulin release and ineffective glucose disposal in target tissues (especially muscles) by insulin (insulin resistance) and metformin affect all these Biophases.^30-32^

Secondary outcomes to be measured include glycaemic profile (measured by FBG, 1HPG, and HB1AC), fetal birth weight, maternal weight gain and caesarean section rate which are expected to be lower in the metformin group, number of NICU admission which is expected to be higher in the insulin group. If found to be effective it may form the basis for developing a policy for Diabetes Mellitus care in pregnancy at primary and secondary level of healthcare instead of the current tertiary level of care.

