**ABSTRACT**

**Background:** Diabetes mellitus is an important complication of pregnancy with adverse effects on both mother and fetus. Poor control of pre-gestational diabetes during the period of organogenesis increases the risk of major congenital malformations. While insulin is effective in controlling high blood glucose levels, otherwise resistant to diet and exercise management, several factors hinder its use. Metformin has been found to be a convenient, cheap, effective and safe hypoglycaemic agent in some countries and it is likely to do same among Ghanaian women.

**Aim:** The main aim of this study is to determine if metformin monotherapy or metformin in combination with insulin is equally effective at attaining and maintaining glycaemic targets compared to insulin monotherapy in the management of gestational diabetes mellitus and type 2 pre-gestational diabetes mellitus in Ghanaians.

**Methodology:**  A prospective randomized comparative study is proposed. Patient selection and randomization will be done using balloting with opaque envelopes. Participants will be followed through their index pregnancy with 2-weekly glycaemic profile monitoring and maternal weight gain. Babies delivered will be followed till the sixth week post-delivery measuring birth weight, incidence of birth trauma and neonatal intensive care unit (NICU) admission rates. Both laboratory and clinical data will be recorded and analyzed.

**Expected outcome:** It is expected that pregnant diabetics treated with metformin will have a lower 2HPG levels at the end of the study than those treated with insulin. The 2-hour post prandial glucose (2HPG) level is the measure selected to estimate the effectiveness of glycaemic control.

In addition NICU admissions are expected to be higher in the insulin group than metformin group.

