**METHODOLOGY**

STUDY DESIGN

The study design is a prospective, randomized comparative study. Participants will be randomly assigned into one of the two treatment groups. For a set of four (4) patients seen at the clinic for the first time, they will be made to ballot by picking randomly one paper with an inscription each from an opaque envelope. This assigned participants to one of the two treatment groups – insulin and metformin. This will be repeated till the sample size is attained. The sequence of picking will be in the order in which they reported to the clinic; “first to report, first to pick”**.**  The participants in each group will be matched for age, parity, gestational age, pre-treatment weight and pre-treatment glycaemic profile.

Treatment will be administered to each according to the study treatment protocols. Subjects in both groups will follow the routine antenatal schedule and their blood glucose levels will also be checked and recorded during these visits according to existing protocols. For in-patients a similar routine will be followed.

STUDY AREA

The study will be conducted at the Maternity Unit and the Diabetes Centre of Korle Bu Teaching Hospital. It will involve both in- patients and out-patients in these units.

STUDY SUBJECTS

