**Insulin group**

In the Insulin group both soluble insulin and premixed insulin will be prescribed. There will be no brand restriction. Both premixed insulin and soluble insulin will be administered subcutaneously in the deltoid region. Total daily dose of premixed insulin at initiation will be calculated for most patients as 0.3 IU/kg body weight. However for patients admitted with high blood glucose levels they will be managed on sliding scale with soluble insulin their starting dose will be based on total daily requirement. The total daily dose will then be divided into two: two-thirds of the dose will be administered in the morning 30 minutes before breakfast and one-third of the daily dose will be administered in the evening 30 minutes before supper. The total dose of insulin will be titrated for each patient to achieve the above glycemic targets. Patients who may not achieve glycemic targets on their out-patient doses after attempts at titrations will be admitted to the ward and treated with soluble insulin to determine their new optimum insulin requirements. All patients will be educated by both nurses and doctors while on admission on the disease and self-administration of the correct doses of insulin before discharge.

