**Treatment failures**

Supplemental insulin for treatment failures in the Metformin group will be prescribed according to the same protocols in the insulin group.

DATA COLLECTION

Basic demographic data will be recorded. They will be followed through their index pregnancy, with 2-weekly blood glucose checks in hospital. All laboratory samples will be collected and analyzed at the diabetes research laboratory by staff of the same laboratory. Venous blood will be used for blood glucose profile analysis. Analysis of Fasting Blood Glucose (FBG), one- hour post-prandial glucose (1HPG), two- hour post-prandial glucose (2HPG) will be done using the Mindray BS-400^®^ (Mindray Medical Int. Ltd, China) chemistry analyzer. The method for glucose determination will be enzymatic photometric testing. Urinalysis, weight records (using Seca^®^(gmbh&Co. Kg Germany)) and cost of treatment will also be documented. The optimal dose of metformin required for optimal glycaemic control will be recorded for each patient. Peri-partum events like gestational age at delivery, type of delivery, fetal birth weight, and NICU admissions will be retrieved from patient notes.

STATISTICAL ANALYSIS

In analyzing the data, summary statistics will include appropriate tables and charts. Categorical data will be represented by pie and bar graphs and continuous data with histograms.

For inferential statistics, significant difference of mean observations using one-tail student’s t-test and z-score for differences in proportions where applicable. The differences in trends of glycaemic profile over time between the study groups will be assessed by two-way repeated measures analysis of variance (ANOVA).

Significance level (p-value) will be set at α = 0.05. Data analysis will be done using statistical package for social science **(SPSS** version 20).

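### NICU admission and caesarean section are staff decisions taken from notes in a trial that describes no masking, so crude differences could reflect knowledge of treatment and not the condition of mother or baby

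*Protocol*

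**What the plan says.** Under EXPECTED OUTCOME, the protocol lists several secondary outcomes with a predicted direction. Two are events: "caesarean section rate which are expected to be lower in the metformin group", and "number of NICU admission which is expected to be higher in the insulin group". The ABSTRACT repeats the second: "In addition NICU admissions are expected to be higher in the insulin group than metformin group".

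The source of both is given under DATA COLLECTION: "Peri-partum events like gestational age at delivery, type of delivery, fetal birth weight, and NICU admissions will be retrieved from patient notes". No criterion for either event, no field for its indication, no masked extraction and no adjudication is mentioned there or elsewhere in the protocol.

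On design, METHODOLOGY says only "The study design is a prospective, randomized comparative study". Neither blinding nor placebo is described. Of the women it says "they will be made to ballot by picking randomly one paper with an inscription each from an opaque envelope", so each can read her own assignment. Metformin is oral; in the other arm, "Both premixed insulin and soluble insulin will be administered subcutaneously in the deltoid region".

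The Metformin Group section takes women who receive supplemental insulin out of the metformin group and analyses them as treatment failures. STATISTICAL ANALYSIS names a one-tail t-test for means and a z-score for proportions, at a significance level of 0.05.

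**The concern.** A laboratory glucose value does not depend on who knows the treatment. Admitting a baby to NICU or delivering by caesarean is a judgement, made here by staff who can see whether the mother was on injections or tablets. If only the fact of admission and the type of delivery are extracted, a baby admitted as a precaution counts the same as a sick baby, and a caesarean booked because of the mother's treatment counts the same as one done for an obstetric problem.

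A difference in crude rates could therefore arise with no difference in the condition of mothers or babies. Because the protocol predicts the direction in advance, such a difference would look like confirmation. The EXPECTED OUTCOME section adds that the results may support a policy for care at primary and secondary level, so a misread secondary outcome could carry weight.

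Removing supplemental-insulin users from the metformin group makes the contrast sharper. What remains is a group with no insulin use, so any staff response to insulin would fall wholly on the comparator.

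**Working it through.** The protocol gives no event rate, power or precision for NICU admission or caesarean, so there is no planned figure to reproduce. The check asks how often a comparison of proportions would favour metformin if the drugs did not differ and only precautionary admissions did. NICU admission is used as the example.

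**Inputs from the protocol.** Recruited number per arm: 52, set from 47 plus 10% for non-response (SAMPLE SIZE DETERMINATION). Significance level: 0.05. Test: z for proportions, sidedness not clearly stated, so both readings are shown.

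**Assumptions, not in the protocol.** Illness-related admission rate b, the same in both arms: 10% or 20%. Share of the remaining insulin babies admitted only for observation, o_I: 10% or 15%. The same share on metformin, o_M: 0% or 5%.

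**Formulae.** The admission rate in an arm is p = b + (1 − b) × o. With X_I and X_M admissions among n = 52 per arm, z = (X_I/n − X_M/n) / √[p̄(1 − p̄) × 2/n], where p̄ = (X_I + X_M)/(2n). The chance of a result favouring metformin is the sum of the two binomial probabilities over all pairs (X_I, X_M) with z > 1.645 (one-sided 0.05) or z > 1.96 (upper tail of a two-sided 0.05 test).

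**Example.** With b = 20%, o_I = 10% and o_M = 0: p_M = 0.20 and p_I = 0.20 + 0.80 × 0.10 = 0.28. The sum is 0.250 one-sided and 0.160 two-sided.

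| b | o_I | o_M | p_I | p_M | One-sided | Two-sided, favouring metformin |
|---|---|---|---|---|---|---|
| 20% | 10% | 0 | 0.280 | 0.200 | 25% | 16% |
| 20% | 15% | 0 | 0.320 | 0.200 | 41% | 29% |
| 10% | 10% | 0 | 0.190 | 0.100 | 36% | 25% |
| 10% | 15% | 0 | 0.235 | 0.100 | 59% | 46% |
| 20% | 10% | 5% | 0.280 | 0.240 | 12% | 7% |
| 20% | 15% | 5% | 0.320 | 0.240 | 24% | 15% |
| 10% | 10% | 5% | 0.190 | 0.145 | 15% | 9% |
| 10% | 15% | 5% | 0.235 | 0.145 | 32% | 21% |

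With equal rates in the two arms the same calculation gives about 5% one-sided and 2.5% two-sided.

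Two things drive the table: the gap between arms in precautionary admission, and the sidedness of the test. The upper four rows assume that no metformin baby is ever observed as a precaution. The lower four relax that by 5% and cut the error by roughly half. The protocol informs neither o_I nor o_M.

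**The case against.** The strongest objection is that the causal step is undocumented. A reader might infer that insulin treatment triggers NICU observation or caesarean at this hospital, so that the crude rates will be biased towards metformin. The protocol does not support that: it contains no admission or caesarean policy. Bias could also run the other way, since the PROBLEM STATEMENT calls metformin use in Ghana controversial, and staff might watch metformin babies more closely. This objection stands. What remains is that crude counts cannot separate the explanations.

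A reader might also take the planned z-test as one-sided and quote only 25–59%. In STATISTICAL ANALYSIS the one-tail label is attached to the t-test and does not clearly reach the z-score. Those figures also assume no precautionary admissions on metformin, although every participant is diabetic and met the criteria for starting insulin. Both points stand, which is why the full range is needed.

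The DATA COLLECTION list is worded as examples, and no data form is shown, so it cannot be said that indications will definitely not be collected; only that the protocol does not ask for them. Crude admission and caesarean rates by assigned treatment are also legitimate measures of what a treatment strategy leads to, including resource use, and a directional expectation is not in itself an error. That argues for keeping the crude counts, not for reporting them alone.

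Finally, both outcomes are secondary and appear in neither the hypotheses nor the specific objectives. That limits the weight of the point without removing it.

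**Conclusion.** The concern holds as a risk to interpretation, not as a demonstrated bias. The protocol supports four facts: both outcomes are staff decisions, both come from notes, no masking is described for visibly different treatments, and both are predicted to favour metformin. Removing supplemental-insulin users from the metformin group would sharpen any effect of staff knowledge. On these facts a crude difference could not be attributed to the condition of mothers or babies.

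The size rests wholly on assumed rates. Under those in the table, the chance of a false result favouring metformin lies between 7% and 59%, depending on sidedness and on how many metformin babies are also observed, against about 2.5% or 5% with no such bias. If metformin babies were observed more often than insulin babies, the bias would be in the opposite direction. The primary outcome, a laboratory 2HPG value, is not affected by this point.

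**What to change.** At the notes retrieval already planned:

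- Record the indication for every NICU admission and every caesarean, and have it classified, where possible, by someone who does not see the arm.
- Compare all women by assigned arm, keeping those who received supplemental insulin in the metformin arm for these outcomes.
- Report the crude counts alongside admissions for a recorded neonatal problem and caesareans by indication, with observation-only admissions shown separately.
- State whether the z-test is one- or two-sided.
- State that both outcomes, including the recorded indication, remain open to staff knowledge of treatment.

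The last statement is needed because the indication is written by the same unmasked staff. Recording it reduces the problem but does not remove it.

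The cost is one extra field per event from notes that are being read anyway, some effort to arrange masked classification, and fewer events in the illness-related count, hence less precision there. No treatment or clinical rule changes.

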**BENEFICIARIES**

MOH, GHS, Diabetes services, Diabetologist; Obstetricians and diabetes healthcare providers as well as all women whose pregnancies maybe complicated by diabetes mellitus.

**DISSEMINATION OF RESULTS**

Results from the study will be presented to the department of pharmacology, University of Ghana Medical School at the M. Phil seminars I & II. It will also be compiled into a thesis and presented to the School of Graduate studies, University of Ghana. Copies will be distributed to various libraries. Findings will also be published in a recognized scientific journal.

**ETHICAL CONSIDERATIONS**

A written informed consent will be sought from all participants. Confidentiality of participants’ data will be assured. Standard protocols for clinical research involving human subjects will be strictly observed.

Data collected will be used for purely research purposes and completed questionnaire will be destroyed upon successful completion of the study.

This proposal will be submitted to Ethical and Protocol Review Committee of University of Ghana Medical School for review and approval.

**BUDGET**

| **ITEM** | **COST (GH ¢)** |
| --- | --- |
| Supplies, Reagents and consumables | **1500** |
| Transportation | **1000** |
| Printing and binding | **200** |
| Stationery | **100** |
| **TOTAL** | **2, 800** |

**ACTIVITY SCHEDULE**

| ACTIVITIES | DURATION: MAY 2012 –MAY 2013 | | | | | | | | | | | | |
| --- | --- | --- | --- | --- | --- | --- | --- | --- | --- | --- | --- | --- | --- |
|  | **May** | **Jun** | **Jul** | **Aug** | **Sep** | **Oct** | **Nov** | **Dec** | **Jan** | **Feb** | **Mar** | **Apr** | **May** |
| Proposal  Writing | * | * | * | * | * | * |  |  |  |  |  |  |  |
| Proposal Presentation at Pham Dept. |  | * |  |  |  |  |  |  |  |  |  |  |  |
| Preliminary workAcquisition of Materials and recruiting participants |  |  | * | * | * |  |  |  |  |  |  |  |  |
| Actual work of participant follow-up and data collection,  Processing/Analysis |  |  |  | * | * | * | * | * | * | * |  |  |  |
| Data Analysis |  |  |  |  |  |  |  | * | * | * |  |  |  |
| Write up | * | * | * | * | * | * | * | * | * | * | * | * |  |
| Presentation of  Research Findings to Pham Dept. |  |  |  |  |  |  |  |  |  |  |  | * |  |
| Submission of  Thesis |  |  |  |  |  |  |  |  |  |  |  |  | * |

